#### Secondary endpoint analysis

For continuous variables, the secondary endpoints will be compared between the control and intervention groups using the same approach as the primary endpoint.

The diagnostic prediction performance of the AI software alone compared with the reference diagnosis by the pulmonologists will also be reported.

#### Subgroup analysis

Subgroup analysis will be performed on the 20 spirometry traces where the confirmed diagnosis (reference standard) was COPD, as spirometry in primary care is most relevant to COPD diagnosis.

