### Procedure

Study participants (participating clinicians) will independently assess the same 50 spirometry records, in the same order, through a bespoke designed online platform developed using Qualtrics XM (Seattle, USA). Participants will be blinded to the reference standards. See figure 1 for example. The patient spirometry records were randomly selected from a database comprising 1122 patients undergoing spirometry in primary care and community-based respiratory clinics in Hillingdon borough between 2015 and 2019. An online randomiser will be used to select the 50 spirometry sessions used in the trial (https://www.randomizer.org/), according to ‘disease category’ so that of the 50 spirometry traces selected, 40% will be from patients with COPD, 20% will have normal spirometry and 10% for each of the four other disease categories (asthma, interstitial lung disease (ILD), other obstructive, other disease/unidentifiable category), to represent a likely distribution of diagnoses in a primary care setting.

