### Study outcomes

The primary endpoint for a primary care clinician participant is the performance of their preferred diagnosis, defined to be the number of correct cases identified expressed as a percentage out of the total number of spirometry records. A correct case is where the participant’s preferred diagnosis matches the reference final diagnosis (described earlier). The secondary endpoints, expressed per participant are listed in table 1.

**Table 1 T1:** Secondary endpoints

Secondary endpoints	Definition	Measured	Reference standard
Quality assessment of the spirometry trace	A correct case is where the participant’s quality grade matches the reference quality grade. Units will be percentage of total cases that are correct	Multiple choice categories: acceptable (grade A/B) or not acceptable (grades C/D/E/F/U)	Respiratory physiologist
Quality assessment self-rated confidence		Visual analogue scale (0–10) where is 0=not confident at all; 10=very confident	
Pattern interpretation of the trace	A correct case is where the participants’ selected pattern matches the reference pattern. Units will be percentage of total cases that are correct	Multiple choice categories: normal, airflow obstruction, possible restriction or non-specific pattern, possible mixed disorder	Respiratory physiologist
Pattern interpretation self-rated confidence		Visual analogue scale (0–10) where is 0=not confident at all; 10=very confident	
Differential diagnostic performance	A correct case is where the preferred or differential diagnosis matches the reference final diagnosis. Units will be percentage of total cases that are correct	Multiple choice categories: asthma, chronic obstructive pulmonary disease, interstitial lung disease, normal lung function, other obstructive disease and other unidentifiable disease	Pulmonologist
Diagnostic self-rated confidence		Visual analogue scale (0–10) where is 0=not confident at all; 10=very confident	

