### Sample size calculation

The sample size calculation was informed by previous feasibility data from 30 primary care practitioners assessing five spirometry traces. The preferred diagnosis matched the reference diagnosis in a mean (SD) of 55% (19%) of spirometry records. We have assumed the same SD of 19%, which is conservative because more cases will be assessed per practitioner, leading to less variable practitioner rates. As the calculation involves conservative assumptions, the power was set below 90%, to be 85%. With 132 participants (66 per group) this allows for detection of a 10% difference (a mean of 5 extra cases in 50) in the rate of cases correctly identified to match the reference standard (mean 65% vs mean 55%) using an unpaired t-test at the two-sided 5% significance level.

The recruitment target was originally estimated at 156 practitioners to allow for an estimated 15% drop out. However, a preliminary analysis of completion rate of the first 50 recruited participants demonstrated that 29 of the 50 participants scored all 50 spirometry records within the 8-week study period (58% completion). Based on this data, the study statistician advised increasing the recruitment target to 228 to account for 42% non-completion (see the Amendment section).

Descriptive statistics will be performed for demographics, baseline characteristics and endpoint data: number and percentage for categorical data and mean and SD or median and interquartile range (IQR) for non-normally distributed continuous data.

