#### Primary endpoint analysis

For each participant, diagnostic performance will be calculated as percentage of the 50 spirometry procedures where the final diagnosis was correctly identified. In each randomised group, the diagnostic performance will be summarised as the mean of the participants’ diagnostic performance. A two-sample unpaired t-test will be used to assess the mean difference in correct response between the two randomised groups. The assumptions for the two-sample t-test will be tested and where the assumption for equal variances fails then the Welch t-test will be used.

Randomisation will be stratified according to job role (GP: yes or no) and Accreditation from Association for Respiratory Technology and Physiology (performance only, interpretation only, performance and interpretation, no accreditation), therefore an analysis of covariance will be used to compare the intervention and control groups by adjusting for the main effects of the stratified variables. To internally validate the estimate of the difference between the two groups bootstrap estimation of difference will be done by taking 100 from the analysis of covariance model or Welch's t-test.

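### For the diagnostic endpoints, the COPD subgroup analysis measures sensitivity only, so it cannot tell better COPD recognition from more frequent COPD calling

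*Protocol article*

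**What the plan says.** The Subgroup analysis section of the protocol article is a single sentence: "Subgroup analysis will be performed on the 20 spirometry traces where the confirmed diagnosis (reference standard) was COPD". The reason it gives is "as spirometry in primary care is most relevant to COPD diagnosis". It names no endpoint.

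The Procedure section fixes the case mix of the 50 traces: "40% will be from patients with COPD, 20% will have normal spirometry and 10% for each of the four other disease categories". The Study outcomes section defines the scoring: "A correct case is where the participant’s preferred diagnosis matches the reference final diagnosis". The primary endpoint uses every trace: "diagnostic performance will be calculated as percentage of the 50 spirometry procedures where the final diagnosis was correctly identified".

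Table 1 adds a differential diagnostic endpoint, which counts a case as correct if either the preferred or the second-choice diagnosis matches. The Secondary endpoint analysis section adds the performance of the AI software on its own. The article does not mention false COPD calls, specificity or predictive value for clinicians by arm.

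**The concern.** The subgroup is chosen for its relevance to diagnosing COPD, and diagnosing COPD means separating it from what is not COPD. A set made up only of reference-COPD traces contains no opportunity for a false positive. If the AI report makes clinicians readier to answer COPD, the subgroup result improves whether or not they have become better at telling COPD from asthma, other obstructive disease or normal lung function.

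What is at stake is the interpretation of one analysis. A positive result could be presented as better COPD diagnosis when the analysis shows only that more COPD cases were called COPD.

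**Working it through.** **The plan's own count.** COPD traces: 0.40 × 50 = 20, which matches the Subgroup analysis section. Non-COPD traces: 0.20 × 50 + 4 × 0.10 × 50 = 10 + 20 = 30, including 5 asthma and 5 other obstructive.

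**What the subgroup measures.** With every reference diagnosis equal to COPD, percent correct = P(answer COPD | reference COPD) = sensitivity. A participant who always answers COPD scores 20/20 = 100% in the subgroup, 0/30 = 0% specificity and 20/50 = 40% on the primary endpoint. Naming COPD first or second on every trace likewise scores 100% on the differential endpoint in this subgroup.

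**Illustration of size.** Inputs:
- Accuracy of 55%. The Sample size calculation section says "The preferred diagnosis matched the reference diagnosis in a mean (SD) of 55% (19%) of spirometry records". Applying 55% to every category is an assumption, because the article gives no per-category accuracy.
- False COPD calls on non-COPD traces of 15%, range 9% to 30%. This is also an assumption.
- A fraction s of all answers is switched to COPD regardless of the trace, which adds no discrimination.

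Formulas: sensitivity = 0.55 + 0.45s; specificity = (1 − false-call rate) × (1 − s); accuracy on non-COPD traces = 0.55 × (1 − s); accuracy on all 50 = (20 × sensitivity + 30 × non-COPD accuracy) / 50.

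With s = 0.20:
- Subgroup result: 0.55 + 0.45 × 0.20 = 0.64, up 9 points from 55%.
- Specificity: 0.85 × 0.80 = 0.68, down from 85%. Over the range: 0.91 × 0.80 = 0.728 (91% to 73%) and 0.70 × 0.80 = 0.56 (70% to 56%).
- Balanced accuracy at a 15% false-call rate: (0.55 + 0.85)/2 = 0.70 before and (0.64 + 0.68)/2 = 0.66 after.
- All-50 accuracy: (20 × 0.64 + 30 × 0.44)/50 = (12.8 + 13.2)/50 = 0.52, down from 55%.

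With s = 0.10 and 0.30 the subgroup gain is 4.5 and 13.5 points. For scale, the trial is sized for a 10-point difference on the primary endpoint.

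**How far the primary endpoint protects.** If the 20% switch affects only the 20 COPD traces and the 10 asthma and other obstructive traces, all-50 accuracy is (20 × 0.64 + 10 × 0.44 + 20 × 0.55)/50 = (12.8 + 4.4 + 11)/50 = 0.564. The primary endpoint then rises slightly, from 55% to 56.4%, while false COPD calls on those 10 traces go from 15% to 1 − 0.85 × 0.80 = 32%. This shift spares the other non-COPD traces, so it is not wholly uninformative, but it adds nothing to separating COPD from the other obstructive conditions.

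**The case against.** - **The primary endpoint is a safeguard.** It counts every false COPD call as wrong. Always answering COPD scores 40%, below the 55% planning mean, and indiscriminate over-calling lowers the result. Even in the obstructive-only case, a rise of 1.4 points would sit beside a subgroup rise of 9, and a careful reader would notice. This stands in part: the primary endpoint pools six categories and never shows COPD specificity.
- **Accuracy on the other 30 traces can be recovered by subtraction.** For complete responders it is (50 × primary − 20 × subgroup)/30; in the illustration, (26 − 12.8)/30 = 0.44. That is accuracy, not COPD specificity. An asthma trace wrongly called other obstructive and then switched to COPD leaves accuracy unchanged but costs specificity. The subtraction also depends on complete data, and the Missing data section admits participants with 70% completion.
- **A subgroup gain may be real.** Suppose COPD calls rise from 65% to 80% on COPD traces, and from 30% to 50% on the 10 asthma and other obstructive traces. Sensitivity gains 15 points. Specificity loses 2/30 = 6.7 points, and balanced accuracy rises (15 − 6.7)/2 = 4.2 points. The subgroup then has the right sign and overstates only the size. This stands: the design leaves the two explanations unseparated, but does not make a subgroup gain false.
- **No endpoint is named.** Technical quality and pattern are scored against other references, so they are not affected. This stands, and it confines the point to the diagnostic endpoints, which the stated rationale suggests are meant.
- **The SAP may add specificity.** It may. But restricting the analysis to reference-COPD traces is a rule the article itself states, not a detail it omits.

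A reader might infer that the AI over-calls COPD. Nothing in the document shows this.

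**Conclusion.** The point holds for the diagnostic endpoints of one subgroup analysis. Percent correct on the 20 traces equals sensitivity, which follows from the stated definitions and needs no assumption. Sensitivity is a legitimate quantity, but alone it cannot support a conclusion about COPD diagnosis.

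The possible size is illustrative: an apparent gain of 9 points with a 17-point loss of specificity. It rests on uniform 55% accuracy, a 15% false-call rate and a 20% indiscriminate switch, none of which the article establishes at category level.

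A reader might go further and infer that the trial's main comparison is biased, or that a positive subgroup result would hide worse discrimination. The document supports neither. The primary endpoint uses all 50 traces, the sample size does not rest on the subgroup, and a subgroup gain can accompany a true improvement. This is a cheap improvement to one analysis, not a defect in the main comparison.

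**What to change.** Keep the 20-trace analysis, but call it sensitivity for COPD. For each participant, add specificity: the percentage of the 30 non-COPD traces where the preferred diagnosis is not COPD. Compare both between arms by the method already planned for continuous endpoints, and state that any conclusion about COPD diagnosis rests on the two together. Name the endpoints to which the subgroup applies. Fix this before any comparison between arms is seen.

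Every participant is already asked for a preferred diagnosis on all 50 traces, so no new data and no change in sample size are needed. The cost is a sentence or two in the analysis plan and one further exploratory comparison, to be labelled as such.

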#### Missing data

Only participants who complete at least 70% of the spirometry cases will be included in the primary analysis. We will compare the baseline characteristics and demographics of those who completed <70% of questions with those who completed ≥70% of questions to identify any systematic differences between completers and non-completers.

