### Statistical analysis

Survey responses from participants will be collated in a secured, online database. A Statistical Analysis Plan will be developed and statistical analysis will be conducted by the study statistician. The statistician will be blinded to control/intervention group allocation. Descriptive statistics will be presented for demographic, baseline characteristics and endpoint data. Number and percentage will be presented for categorical data. Mean and SD will be presented for normally distributed continuous data while median IQR will be presented for non-normally distributed continuous data.

The number of participants consented, randomised, and completing the study will be described in a study Consolidated Standards of Reporting Trials diagram.

Data analysis will be performed on an intention to treat basis. Data will be analysed with the statistical software Stata V.17.0. All statistical tests will be two-sided and significance set at p<0.05.

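### The primary analysis keeps only participants who complete at least 70% of cases, which contradicts the stated intention-to-treat analysis and leaves the result open to selection after randomisation

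*Protocol article*

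**What the plan says.** Under Statistical analysis, the protocol article states without qualification: "Data analysis will be performed on an intention to treat basis". Under Missing data it then sets an entry condition for the primary comparison: "Only participants who complete at least 70% of the spirometry cases will be included in the primary analysis". With 50 records per participant, that means at least 35.

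The same section names one check: "We will compare the baseline characteristics and demographics of those who completed <70% of questions with those who completed ≥70% of questions", in order "to identify any systematic differences between completers and non-completers". It does not mention arm. The threshold is put in terms of cases in one sentence and questions in the next.

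The Eligibility criteria section places 1:1 randomisation at the point of consent, before any record is scored.

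The Sample size calculation section reports that 29 of the first 50 recruits scored all 50 records within 8 weeks (58%). The response was "increasing the recruitment target to 228 to account for 42% non-completion".

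**The concern.** Intention to treat analyses participants as randomised. A rule that admits only those who later finish 35 or more cases gives up that protection. The arms do visibly different tasks: the same 50 records, with or without an AI report, over up to 8 weeks. The report could make the task easier and more engaging, or it could lengthen each case. Either could change how many clinicians reach 35 cases, and which ones.

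If the arms retain different kinds of clinician, part of the difference in diagnostic performance reflects who stayed rather than what the AI did. That could create an apparent benefit or hide a real one. The rule also discards up to 34 answered cases from each excluded participant, although those answers bear directly on the primary outcome.

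The planned baseline comparison can describe selection but cannot correct it.

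**Working it through.** **1. The two rules side by side.** Statistical analysis: intention to treat, with no modified or per-protocol qualifier. Missing data: primary analysis only if at least 0.70 × 50 = 35 cases are completed. Since randomisation comes first, both cannot hold unless every randomised participant reaches 35.

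**2. The plan's own sample size reproduces.** Inputs from Sample size calculation: difference 10 points, SD 19, two-sided 5%, power 85%, unpaired t-test.
- The t-based solution is 65.8, so 66 per arm and 132 in total; power at 66 per arm is 85.1%.
- At 15% drop-out: 132 / 0.85 = 155.3, so 156.
- At 42% non-completion: 132 / 0.58 = 227.6, so 228.

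The target is therefore sized to leave about 228 × 0.58 = 132 participants who finish. This protects power and does nothing about who those participants are.

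**3. How many might be excluded.** Non-completion of all 50 records is 21/50 = 42% (exact 95% CI 28% to 57%). Exclusion applies only below 35, so participants with 35 to 49 cases stay in. The excluded share is not stated; on these data it is at most 42%.

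**4. Size of bias, illustration only.** Let an arm exclude a fraction e, and let retained participants score g points above excluded ones. The arm's overall mean is (1 − e) × retained mean + e × excluded mean, so the retained mean exceeds the overall mean by e × g. Assume no true effect, e = 0.42 in both arms, and a gap in one arm only:
- g = 5: bias 0.42 × 5 = 2.1 points.
- g = 10: bias 0.42 × 10 = 4.2 points.

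The standard error at SD 19 and 66 per arm is 19 × √(2/66) = 3.31. Type I error is 1 − Φ(1.96 − bias/SE) + Φ(−1.96 − bias/SE), which gives:
- 2.1 points: about 9.7%.
- 4.2 points: about 25%.

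**5. Sensitivity to the assumptions.**
- Smaller excluded share: e = 0.20 leaves about 114 × 0.80 = 91 per arm, SE 19 × √(2/91) = 2.82. The biases are 1.0 and 2.0 points, with type I error about 6% and 11%.
- Smaller SD: the protocol calls 19 conservative. With an assumed SD of 10, e = 0.42 and 66 per arm, SE = 1.74, and type I error is about 23% and 67%.
- Same gap in both arms but unequal retention (assumed 68% and 48%): bias is (0.52 − 0.32) × g, so 1.0 point for g = 5 and 3.8 points for g = 19.
- Same gap and same retention in both arms: the bias cancels.

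**6. Power without the exclusion.** With all 228 analysed (114 per arm), a 10-point difference and SD 19, power is 97.7%. If the 42% showed no benefit at all (an assumption), the difference would be 0.58 × 10 = 5.8 points and power about 63%.

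**The case against.** Several points on the other side have force.

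- **The 42% is not the excluded share.** A reader might infer that about four in ten randomised participants will be dropped. The documents do not support this, because 42% is the share short of 50 records, not of 35. It is only a ceiling on these data.
- **No evidence of differential selection.** A reader might infer that the AI report will change completion, or that type I error will reach the highest values above. The article gives no completion by arm or by ability and no SD other than 19. The figures are illustrations, and the bias could be nil.
- **The baseline check may be done by arm.** A reader might infer that it pools the arms. The article does not say so, and the statistical analysis plan may tabulate it by arm and hold sensitivity analyses. The planned CONSORT diagram may also show completion by arm.
- **Cases or questions.** Every case carries the same question set, so the two wordings differ only for partly answered cases. This is a minor point of wording.
- **The remedy is not full intention to treat.** Requiring at least one answered case is also a condition met after randomisation. A case-level model reduces this kind of bias without removing it, and other models would serve.

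All of these stand as limits on size and wording. None removes the conflict between the two sentences, which are both current text. An unseen analysis plan cannot satisfy both as written.

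**Conclusion.** The contradiction is established from the article alone: the primary analysis set is defined by behaviour after randomisation and is labelled intention to treat. It should be fixed because it decides who enters the primary comparison.

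The direction and size of any bias are unknown. A bias of 2.1 to 4.2 points, with type I error of about 10% to 25%, rests on four assumptions: 42% excluded in each arm, a gap of 5 to 10 points in one arm only, SD 19, and 66 analysed per arm. With fewer excluded the error is smaller; with a smaller SD it is larger. For scale, the trial is designed to detect 10 points. The larger recruitment target does not reduce this bias.

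**What to change.** - **Primary analysis.** Include all randomised participants with any answered case, in the arm assigned, using all answered cases. One suitable choice is a case-level mixed model with arm, the minimisation factors, case effects and a participant random intercept. Records are shown in the same order, so partial completers may have answered a different mix of cases; the case effects allow for that. Report the result as a difference in percentage points so that it can be read against the design difference of 10.
- **Sensitivity analyses.** Keep the set with at least 70% complete, labelled as a completer analysis. Add an analysis covering randomised participants with no answers, since the any-answer set is not full intention to treat.
- **Description.** Compare the characteristics of included and excluded participants by arm.
- **Definition.** Use one measure of completion throughout: the number of cases with a preferred diagnosis answered.
- **At minimum.** Drop the intention-to-treat label for the 70% set and report the all-participants analysis beside it.

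The cost is mainly wording. Responses are captured on the online platform, and applying the 70% rule already needs a count of completed cases, so no new data collection is evident. The primary model becomes slightly more complex than a t-test, and the bias is reduced rather than removed. The recruitment target need not rise if the 10-point difference holds across all participants; if those who stop early gain nothing, power would be lower, as shown above.
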